## Abstract

**Introduction:**

Academic fraud is any behavior that gives a student an undeserved advantage over another student. Few studies have explored the causes of and possible solutions to academic fraud in Latin America. We aim to map the knowledge of stakeholders in a Colombian faculty of medicine about the factors that facilitate and prevent academic fraud.

**Methods:**

Fuzzy cognitive mapping. We will use the approach proposed by Andersson and Silver to generate fuzzy cognitive maps representing stakeholder knowledge. This process consists of ten steps: (1) definition of the research question; (2) identification of participants; (3) generation of ideas; (4) rationalization of ideas; (5) organization and connection of ideas; (6) weighing; (7) pattern grouping; (8) list of links and digitization; (9) combination of maps and network analysis; and (10) deliberative dialogue. To draw the maps, we will invite medical students, interns, resident physicians, master’s students, and professors in the faculty of medicine. Four medical students will receive training to facilitate the sessions. Participants will identify the factors contributing to academic fraud and their causal relationships. We will use a combination of network analysis and graph theory to identify the chains of factors with greatest influence on academic fraud.

**Conclusion:**

The maps will serve to discuss strategies to reduce academic fraud in the Faculty of Medicine and to identify factors that could be addressed in other contexts with similar problems. This research will allow the students who facilitate mapping sessions to learn about research techniques, fuzzy cognitive mapping and academic fraud.

**Study registration:** Registered in OSF Registries on August 2nd, 2022. Registration number: osf.io/v4amz

## Introduction

Although there is no globally accepted understanding of academic fraud [1], a widely used definition is any behavior that gives a student an unearned or undeserved advantage over another student [2, 3]. Among the health sciences, academic fraud includes copying others, using false clinical notes, sharing information about exams, and lying about physical exams performed on patients [4]. Fraud can be active when the goal is to gain a benefit for the student themselves or passive when the goal is to help a partner [5]. Since there are important differences between medical schools around the world, the definition of fraud must be flexible, progressive, and tailored to the local context in which they operate [6, 7]. For example, fraud practices have evolved as technology has come to play a critical role in academic life [7], which has been particularly important in the context of the Covid-19 pandemic.

Academic fraud is a frequent phenomenon. For example, the prevalence of fraud has been estimated to be as high as 58%in medical schools in the United States [4]. Unfortunately, academic fraud in the health sciences leads to potentially serious consequences. In medicine, academic fraud during student life has been reported to be associated with disciplinary problems during professional life [8]. Fraud also has economic consequences. In 2012, the U.S. Institute of Medicine estimated that the National Health System loses $765 billion annually due to administrative malfunction, which includes $75 billion due to fraud [6]. An example of fraud is the case of California doctors issuing bills for the same drugs multiple times [9].

In Colombia, a study based on data collected from 2003 to 2013 among four top universities found that more than 90% of students admitted having engaged in fraud in their academic life [7]. This study also identified types of academic fraud committed in the country, such as letting another student copy on an exam, including the name of a student who did not work in the assignments, lending an assignment (passive fraud), impersonation in an exam, downloading assignments from the internet, or using specific tools (like calculators) when it was not allowed (active fraud).

The factors promoting academic fraud have been also classified as intrinsic and extrinsic [10]. Intrinsic factors are characteristics such as gender, self-esteem, level of maturity, moral development, and academic performance. The extrinsic factors comprise the systems of institutional (legal) control, as well as the cultural and moral environment. Martínez et al. [7] described the perception of cost-benefit facilitating fraud: students perceive a low risk of being detected or sanctioned and simultaneously important benefits if they succeed in their attempt. In Colombia [7], these researchers reported reasons why students commit fraud such as concerns about the grade point average, memory-oriented exams and evaluations, poor quality of teaching, a poorly understood exam, burnout, and a desire to help a friend. Additionally, factors such as the desire to learn, considering fraud as something dishonest, and feeling bad about committing fraud were identified as protectors against fraud.

Different authors and monitoring entities agree that health professionals, including doctors and medical students, should receive training in academic integrity to prevent fraud [6, 11]. In the United States, for example, the objective of these programs is to prevent fraud, abuse, errors and waste of resources [6]. Similarly, there is consensus that training programs should be directed simultaneously at medical students and professors, to achieve a synergistic effect [11].

Little research has addressed the causes and consequences of academic fraud in Latin America [7]. The few existing fraud prevention programs, much more common in North America, are focused on educating healthcare professionals on administrative aspects related to paying reimbursements for services [6, 11]. This study aims to map the knowledge of stakeholders in a Colombian faculty of medicine about the factors that facilitate and prevent academic fraud.

## Methods

### Setting

We will conduct the study at the Faculty of Medicine of La Sabana University in the municipality of Chía, Colombia. Chía is located 15 km from Bogotá, the capital of Colombia. La Sabana University is a private institution that currently offers 23 undergraduate and 99 graduate programs [12].

The university has 8,926 undergraduate students. Some 22% of these students come from a low socioeconomic background, 52% belong to the middle class, and the remaining 26% come from a high socioeconomic level [12]. Currently, there are about 900 students enrolled in the Faculty of Medicine, where the undergraduate medical program lasts seven years.

### Study design

Study uses fuzzy cognitive mapping (FCM), which are commonly used to explore the constellation of factors that contribute to outcomes and to inform health decisions. FCM comprises concepts or nodes (determinants or factors that influence a system of additional factors) and causal links (connections between nodes) which receive a weight according to their relative strength (Fig 1) [13].

**Fig 1 pone.0291737.g001:**
[figure not shown]
Representation of a fuzzy cognitive map. The map comprises concepts or nodes (A, B, C, and D) and weighted causal links (W).

### Study procedures

We will follow the steps proposed by Andersson and Silver [13] to generate fuzzy cognitive maps representing the factors that facilitate or prevent academic fraud. This process consists of ten steps: (1) definition of the research question; (2) identification of participants; (3) generation of ideas; (4) rationalization of ideas; (5) organization and connection of ideas; (6) weighing; (7) pattern grouping; (8) list of links and digitization; (9) combination of maps and network analysis; (10) deliberative dialogue. We describe each of the steps below.

#### Research question

What factors promote or prevent academic fraud at the Faculty of Medicine of La Sabana University?

We will use the definition of academic fraud proposed by Genereux et al. [5] and taken up by Eshet: [3] any behavior that gives a student an unearned or undeserved advantage over another student. The definition is broad and doesn’t distinguish between severity levels of infractions. Infractions’ seriousness can vary based on circumstances and subjective interpretations. Nonetheless, the definition allows participants to align their views with what they consider fraudulent behavior.

#### Participants

Andersson and Silver [13] recommend organizing participants into homogeneous groups of no more than five people to avoid power imbalances and to facilitate discussion in the mapping sessions. We will invite five groups, each consisting of five people, resulting in a total of at least 25 participants. We will make successive maps with additional groups of stakeholders until we achieve qualitative saturation of concepts. Participants will be organized and separated by groups of stakeholders as follows: students from preclinical semesters (I to IV); students from clinical semesters and medical interns (V to XIV); resident physicians; master’s students; and professors of the faculty of medicine.The inclusion criteria are 1. Being a student, intern, resident, master’s student, or professor of medicine of legal age (≥18 years) at the faculty of medicine of La Sabana University; and 2. Having received at least two doses of any COVID-19 vaccine approved in Colombia.

The Faculty of Medicine will contribute to participant recruitment by issuing a call through their message list (S1 File). All students and faculty members associated with the faculty will receive the invitation. Those who wish to take part in the study will register on an online page accessible only to a member of the research team (JP). During registration, each participant will propose their preferred schedule, and the groups will be organized accordingly.

The lead author (JP) will train four research assistants as facilitators of the FCM sessions using the resources found on https://www.ciet.org/fcm. These include an instructional video located at https://www.screencast.com/t/6whTNuRun6W that provides detailed information on how to conduct the sessions. The trainees will conduct supervised practice sessions with volunteers to ensure they adhere to the standardized protocol. The analysis will not include the practice maps. Once the trainees do not need additional corrections, they will start data collection.

Each session will have a facilitator and a reporter to take notes of the discussions. For each session, the number of participants and their characteristics in terms of gender, age, place of origin, semester, and academic background will be recorded.

#### Mapping sessions

Each mapping session will follow these steps:

*1. Generation of ideas*

Using a sheet of whiteboard and *post-its*, the facilitator will place a central node “academic fraud” in the center of the whiteboard and will ask the participants: what does academic fraud mean to you?

After all the participants answer the question, the facilitator will ask what do you consider to be the factors that promote or prevent academic fraud? Participants will have 15 minutes to write concepts in the *post-it*s and will add the concepts that positively or negatively influence the occurrence of the central node. This step may take less time if participants exhaust the concepts sooner than expected.

*2. Grouping of ideas*

The facilitator and participants group related concepts and eliminate duplications. For example, words that mean the same thing but are expressed differently (cell phone and smartphone). This step will help synthesize and clarify the map. Participants will have to reach a consensus and accept each new category created. This step will also be an opportunity to eliminate, redefine, deepen, or even suggest new concepts.

*a. Connection and organization of nodes*

In this step, participants will draw the connections between concepts using arrows to indicate the direction of the cause-effect relationship. Connections can be between concepts and the central node, or between concepts. This step will also be an opportunity to redefine concepts, reshape and improve the map.

*b. Weighing*

Participants will assign a weight to each relationship between nodes to indicate variability in levels of influence. This scale uses numbers to indicate the strength of the relationship and positive or negative signs to represent the direction of its influence. Positive values indicate that the increase of a node will increase another node and negative values indicate the opposite. Weights will be expressed in the range of 1 to 5. Values closer to zero correspond to a weaker level of influence and values closer to five indicate stronger levels of influence.

To establish the weights, once all the arrows are drawn the facilitators will ask: which of all these relationships is the strongest? In other words, on a scale of 1 to 5, what relationship would be a 5? Then the facilitators will ask: which of all these relationships is the weakest? In other words, on a scale of 1 to 5, which relationship would be a 1? After this, the facilitators will ask the participants about the relative weight of the remaining arrows. If there are disputes or differences of opinion between participants, the reasons will be noted and the consequence of each of the alternatives will be established in the final model.

Once all the arrows have received a weight validated by all participants, a photograph of the map will be taken. On the whiteboard, the name of the group, its members, and the date will be noted.

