### Safety considerations

We recognize that the topic covered in this research (academic fraud) is sensitive to participants. However, the research explores the facilitating and preventing factors of fraud, and will not inquire about personal experiences of fraud that participants may have incurred in. We will kindly remind participants not to share any personal experiences of fraud. To guarantee confidentiality, we will not record the sessions, and the note taker will not include any information that could allow us to identify the identity of individuals.

This study employs non-invasive techniques. Based on the above, according to resolution No. 8430 of 1993 of the Ministry of Health of Colombia, the study poses minimal risk to the participants [21]. Similarly, the research is classified as of minimum risk according to the Tri-Council Policy Statement of Canada [20]. This means that the likelihood and magnitude of potential harm from their participation in a study are no greater than those found by the participant in those aspects of their daily lives that relate to the research.

To avoid possible undue influence or coercion with students, a third party unrelated to the research, who has no power or authority over the students, will be present for the consent process. The consent will explain that no sanctions (academic or otherwise) will be generated for not agreeing to participate in the study.

Finally, we will make sure to implement strict measures to prevent the spread of COVID-19. We will only invite participants who have received at least two doses of any COVID-19 vaccine approved in Colombia. Mapping sessions will be held observing hand hygiene practices every 15 minutes. We will ask participants to always wear masks and to maintain a minimum distance of two meters. Finally, each student will use their own materials (pens, post-it) and the circulation of materials among the participants will be discouraged.

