### Data management plan

When digitizing information, we will treat all participant responses as confidential, and we will not record names or identify information along with their responses. A computer with a password will protect the encrypted data, and the physical copies will be secured in a locked cabinet in the lead author’s office at La Sabana University, inaccessible to anyone outside the study. The original paper records will be transported, stored, retained and, after seven years, destroyed following the guidelines of the Center for Research in Tropical Diseases (CIET) [22] for the security, storage and eventual destruction of paper records.

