## Discussion

This study will shed light on the factors associated with academic fraud at a Colombian private university. This information could help to conceive strategies to tackle academic fraud more broadly. To the best of our knowledge, this will be the first study using FCM to explore factors that promote or prevent academic fraud in education.

FCM will allow a participatory approach to identify factors related to academic fraud and to discuss potential solutions with stakeholders. Participatory research includes the promotion of action and contributes to address gaps in both knowledge and practice [25]. It involves co-design and co-ownership of health solutions between researchers and end-users. Collaboration with stakeholders ensures interventions that are aligned to the needs and specificities of end-users, thus improving their reach, adoption, and effectiveness [26]. We will discuss the study results with participants to identify priority areas to be addressed and to generate recommendations for action. Co-designed solutions will be implemented and further investigated through research designs such as a pilot randomised controlled trixsal (not described in this article).

FCM uses graphical language, which our previous research confirms is very accessible across educational and cultural backgrounds [27]. This will facilitate communication of the results across the university or with other groups. Obvious power disparities between faculty and students hinder discussion across the academic community. The use of cognitive maps representing the anonymous views of different stakeholder groups could facilitate dialogue among them. Because the maps do not contain any personal information, we expect that students will feel safe presenting their perspectives and proposals. Even more, we expect that reflecting on fraud could detonate internal dynamics that could promote students to reduce dishonest behaviors.

This project is a student-driven initiative. With the support of advisors (JP, CC, IS) the medical students co-authoring this manuscript (PL, JR, LN, DJ) defined the research question and research methods, and will guide data collection, analysis, and results dissemination.

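### The session procedure lists the group's members on the whiteboard sheet that carries the map, while the Discussion says the maps hold no personal information

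*Protocol article*

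**What the plan says.** The map is built on a physical board (Mapping sessions, step 1: "Using a sheet of whiteboard"). Once participants have agreed all the weights, "a photograph of the map will be taken". The next sentence reads: "On the whiteboard, the name of the group, its members, and the date will be noted".

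Four other sections bear on confidentiality:

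- **Discussion:** "Because the maps do not contain any personal information, we expect that students will feel safe presenting their perspectives and proposals". The same paragraph describes the maps as showing the anonymous views of stakeholder groups.
- **Data management plan:** "we will not record names or identify information along with their responses". The sentence opens with a clause that ties it to digitizing. The section then provides for encryption, a password, a locked cabinet and destruction of paper records after seven years.
- **Safety considerations:** the topic is acknowledged to be sensitive, sessions are not recorded, and "the note taker will not include any information that could allow us to identify the identity of individuals".
- **Ethical considerations:** the study adopts guidelines under which the method must protect the confidentiality of individual students' responses, and research assistants explain the confidentiality of answers at consent.

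**The concern.** The instruction for labelling the board attaches the participants to the record of their views. The Discussion says that record contains nothing personal and rests an expectation on it: trainees will speak freely because the maps cannot point to them. If members are listed on the sheet, that assurance is inaccurate for the source map.

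Two things are at stake. The first is an ethics commitment: a participant who is told at consent that answers are confidential, and then sees the group's members written on the board, has received a statement that the procedure does not honour. The second is candour. The Limitations section lists social desirability bias from power imbalances in medical education as a threat to the trainees' maps. A visible member list works against the safety that the article relies on, although the documents allow no estimate of how much.

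**Working it through.** No figure in the plan depends on this point, so the check is a comparison of texts.

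**1. Does the label sit on the record of responses?** The map is drawn on the whiteboard sheet, and the label goes on the whiteboard. They share one medium.

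**2. Does the label identify people?** The text says that the group's name, its members and the date are noted. It does not say that the members' *names* are noted. Set beside the group's name and the date, a list of people is the natural reading. Codes or a head count are possible, but nothing suggests them.

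**3. Is the label in the photograph?** The photograph is mentioned first and the label second, and the order of the two acts is not fixed. If the label comes first, the photograph shows the members. If it comes afterwards, the members are still listed on the sheet that holds the map.

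**4. Is the list removed later?** No section says that it is coded, cropped, masked or erased before storage.

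**5. Which statements does this contradict?**

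| Statement | Scope | Conflict with the label |
|---|---|---|
| Discussion: maps hold no personal information | The maps, without restriction | Direct |
| Data management plan: no names with responses | Tied to digitizing | Partial: a photograph is arguably a digital record, but the edge list is not affected |
| Ethical considerations: confidentiality of student responses | The method as a whole | The label sits poorly with it |
| Safety considerations: nothing identifying in the notes | The note taker's notes | None: the board label is a different record |

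**6. How many people does it concern?** Status and timeline reports one session with 3 medical students and two sessions with 9 master's students: 3 + 9 = 12 people in 1 + 2 = 3 sessions. The Participants section plans five groups of five, 5 × 5 = 25 people at least. If the procedure is followed as written, all of them are listed as members of a group.

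**7. Does the analysis need the label?** The edge list in FCM analysis has three columns: cause, effect and weight. Maps are combined by stakeholder group. Neither step uses members' identities.

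**The case against.** The strongest defence is that the confidentiality statements refer to other objects. The Data management sentence concerns digitizing, and the digitized product is an edge list with no field for a name. Paper originals are covered separately by locked storage that nobody outside the study can reach. The Discussion sentence appears where the article considers maps used for dialogue between stakeholder groups, which could mean the combined, averaged maps. The maps are also consensus products, everyone in the room already knows who took part, and participants are reminded not to relate personal experience of fraud.

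Part of this stands. The Data management sentence is ambiguous rather than contradictory, and the storage safeguards are real. But the Discussion speaks of the maps without limiting itself to combined or digitized ones, and secure storage restricts access without making the sheet free of personal information.

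A reader might also infer stronger points that the documents do not support:

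- *That names certainly appear in the photographs.* Both the names and the order of labelling and photographing are inferences.
- *That a photograph could reach the faculty.* Deliberative dialogue shares results, maps and tables with participants. No section plans to show source photographs.
- *That the participant details identify people on the map anyway.* The Participants section says that "their characteristics in terms of gender, age, place of origin, semester, and academic background will be recorded", but not that they go on the map. The documents give no distribution of these characteristics from which to calculate uniqueness.
- *That the registration page is itself a breach.* Applicants "will register on an online page accessible only to a member of the research team", which is ordinary restricted administration.
- *That social desirability is the main limitation, or that labelling demonstrably worsens it.* The Limitations section does not rank its items, and in the order written the label follows agreement on all weights.

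**Conclusion.** The concern holds in a limited form. The labelling instruction contradicts the Discussion's statement that maps contain no personal information. It also sits poorly with the Data management plan and with the confidentiality commitment in Ethical considerations. As written, the instruction is wrong and should be changed.

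The size is modest. What is exposed is membership of a small group that produced a consensus map, not individually attributed answers, and access to the originals stays restricted. It would be too strong to say that the study's confidentiality protection has failed: what fails is the anonymity claim for the source map. No estimate, sample size or network measure is affected.

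The conclusion assumes that the word for members means the people themselves. If codes were intended, the remedy is only to say so. Whether member lists exist for the 12 people already mapped cannot be told from the article.

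**What to change.** Replace the labelling sentence in Mapping sessions with, for example: *Only a session code and the stakeholder group will be written on the whiteboard; no participant will be listed. The key that links session codes to dates and participants will be kept apart from the maps and photographs, with restricted access.*

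Check the sheets and photographs from the three sessions already held, and mask any member names found.

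The cost is one sentence, a check of three sessions, and upkeep of a separate key. The key is needed because Deliberative dialogue reconvenes each group, so some record of membership must survive. The edge list, the combination of maps and the centrality measures stay as they are.
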